### Tertiary Efficacy Endpoint

6.3

The change in the ‘metabolic target risk score’ (MeTaRiSc) from baseline to week 84. Each individual will be assigned the value 1 for each parameter above the targets, and the sum of the 3 parameters will be divided by 3. The MeTaRiSc is this weighted mean that varies from 0 to 1.
i.+1 if more than 10% of home SBP measurements ≥ 130 mmHg.ii.+1 point if LDL cholesterol levels are above targets defined by the 2013 ACC/AHA cholesterol guidelines;iii.+1 point if glycated hemoglobin (HbA1c) levels ≥ 7.0%.

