#### Operational Definitions

3.1.1

−Uncontrolled hypertension: mean 24‐h ambulatory blood pressure ≥ 130/80 mmHg, or ≥ 2 office or home BP readings ≥ 130 mmHg systolic and/or ≥ 80 mmHg diastolic recorded in the electronic health record (EHR) within the past 18 months, excluding emergency or procedural visits.−Uncontrolled LDL‐C: (i) LDL‐C ≥ 50 mg/dL in individuals at very high cardiovascular risk; (ii) LDL‐C ≥ 70 mg/dL in individuals at high cardiovascular risk; (iii) LDL‐C ≥ 100 mg/dL in individuals at intermediate cardiovascular risk; (iv) individuals with a history of LDL‐C ≥ 190 mg/dL at any time, according to the 2025 Brazilian Guideline on Dyslipidemias and Atherosclerosis Prevention. Individuals with diabetes mellitus may present cardiovascular risk ranging from intermediate to very high, depending on disease duration, the presence of additional risk factors, or evidence of target‐organ damage.
Exclusion criteria
i.Secondary hypertension or conditions requiring non‐standard management.ii.Participation in another interventional clinical trial.iii.Individuals with active underlying malignancies.iv.Moderate‐to‐severe cognitive impairment or severe psychiatric condition that precludes consent or adherence.v.Inability to use or access a telephone for remote contacts, even with caregiver assistance.vi.Illiteracy that prevents comprehension of informed consent or digital interaction.

The exclusion of illiterate individuals was defined to ensure valid informed consent and reliable participation in remote data collection and digital self‐monitoring. Recruitment occurs in community‐based primary care services serving socioeconomically diverse populations, and results will be interpreted in the context of individuals with functional literacy compatible with digital self‐care within the public health system.

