## Interventions

5

Participants in the control arm will receive treatment at the discretion of their physician, without interference from the study personnel, and they will be followed up through app interactions, phone calls, and lab exams every 24 weeks.

Both study arms are recruited and followed within the same BHU of the Brazilian Primary Health Care Network, ensuring comparable clinical settings and multidisciplinary staff. Usual care in these units is provided by PCPs and nurses and is defined as routine management typically involving in‐person consultations every 3–6 months according to clinical need, with medication adjustments and laboratory testing performed at the physician's discretion, and no structured digital follow‐up. In the control arm, no standardized algorithms or automated decision‐support tools are used, and there are no scheduled tele‐touchpoints beyond those required for data collection. All usual‐care contacts and visit frequencies will be documented to allow comparison of exposure intensity between study arms. To minimize contamination between study arms, the structured remote workflow is delivered exclusively by the trained study monitors assigned to the intervention arm. Control participants do not have access to TAMIS‐IA clinical decision support, automated titration protocols, or structured telemonitoring beyond protocol‐required data collection. Usual care providers remain independent from the intervention workflow, and no algorithm‐driven recommendations are integrated into routine care.

Participants in the active intervention arm will receive treatment based on standardized clinical guidelines, with instructions provided remotely by study monitors under physician supervision. The study monitors are health care professionals and research fellows with clinical backgrounds, specifically trained to conduct structured telephone follow‐ups, data collection, and patient education activities. The intervention is supported by TAMIS‐IA, a web‐based digital health platform that enables remote management, patient monitoring, and clinical decision support. All medication adjustments or new prescriptions generated through the digital platform are reviewed and formally approved by physicians before implementation to ensure clinical safety and protocol compliance. Further technical and operational details of the platform are provided in Supporting Information S1: Material 2.

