**Figure 3 jep70456-fig-0003:**
[figure not shown]
Hypertension management algorithm: treatment initiation, titration, and referral pathways. ACEi, angiotensin‐converting enzyme inhibitor; ARB, angiotensin receptor blocker; BP, blood pressure; CCB, calcium channel blocker; CKD, chronic kidney disease; DM, diabetes mellitus; HBPM, home blood pressure monitoring; HCTZ, hydrochlorothiazide.

A customized software platform was developed to automatically calculate weekly BP averages, defining target BP as a weekly systolic BP (SBP) < 130 mmHg and diastolic BP (DBP) < 80 mmHg. The system allows for dynamic adjustments of BP targets based on individual clinical indications.

For patients whose home BP remains elevated, medication adjustments will be conducted remotely, via telephone consultations with a patient monitor, following the clinical algorithm integrated into the software platform. Physicians will review and approve all new prescriptions before implementation. This approach allows for more frequent medication titrations than in standard clinical practice.

After each titration, patients will wait 1 week for stabilization before repeating another 6‐day BP measurement cycle at home. This results in a biweekly cycle of medication titrations, which aligns with the pharmacokinetics of the prescribed antihypertensive agents, including angiotensin‐converting enzyme (ACE) inhibitors, angiotensin‐receptor blockers (ARBs), calcium channel blockers (CCBs), and diuretics.

This accelerated titration protocol aims to overcome the therapeutic inertia commonly seen in traditional BP management. Throughout the study, electrolytes and renal function will be monitored when clinically indicated. Once patients achieve BP control, they will transition out of the intensive titration phase, moving to a surveillance phase with follow‐ups every 6 months.

If a participant's home BP remains elevated despite the use of three antihypertensive agents, including a diuretic, they will be classified as having resistant hypertension and automatically referred to a SAH specialist for further evaluation and treatment.

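### The MeTaRiSc score does not measure attainment of the trial's own targets: its BP item conflicts with the programme's BP target, and its LDL-C item cites a different guideline

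*Protocol article*

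**What the plan says.** All references are to the protocol article.

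- **Score (6.3).** Each of three parameters contributes 1 if above its target, and the sum is divided by 3. The BP item gives the point when "more than 10% of home SBP measurements" are at or above 130 mmHg. The LDL-C item refers to "targets defined by the 2013 ACC/AHA cholesterol guidelines". The HbA1c item is 7.0% or more.
- **BP target (5.2).** The platform averages home readings over the week, "defining target BP as a weekly systolic BP (SBP) < 130 mmHg and diastolic BP (DBP) < 80 mmHg". Participants who reach control leave intensive titration for six-monthly surveillance. The same section adds: "The system allows for dynamic adjustments of BP targets based on individual clinical indications".
- **Home BP cycle (5.2).** Six consecutive days, with two readings each morning and two each evening.
- **LDL-C.** Section 3.1.1 defines uncontrolled LDL-C as at least 50, 70 or 100 mg/dL for very high, high and intermediate risk, or any history of at least 190 mg/dL, "according to the 2025 Brazilian Guideline on Dyslipidemias and Atherosclerosis Prevention". Section 5.4 and the Figure 5 legend treat by the same 2025 guideline, to targets below 50, 70 and 100 mg/dL.
- **Analysis (9.4).** The change in MeTaRiSc from baseline to week 84 is formally tested, at alpha 0.025.

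**The concern.** A score described as counting parameters above target should use the targets that the trial states. Two of the three items do not, and the article gives no reason.

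For BP, the score counts single systolic readings, while the programme works on a mean and includes diastolic pressure. The BP item can therefore stay at 1 after the programme has declared control and stopped titrating. For LDL-C, participants are enrolled and treated by one standard and scored by another. Only HbA1c is aligned, with the same 7.0% in the inclusion criteria (3.1) and in the score.

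MeTaRiSc is the only tertiary endpoint and combines the three risk factors that the programme manages. As written, a change in it cannot be read as a change in the number of targets met.

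**Working it through.** The article states no power or expected value for MeTaRiSc, so there is no figure to reproduce. The check compares definitions and then works out the consequence for BP.

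**Inputs**
- Readings per cycle (5.2): 6 days × 4 = 24.
- Scoring rule (6.3): more than 10% of readings with SBP at or above 130. Since 10% of 24 is 2.4, the point is given at 3 or more readings (3/24 = 12.5%) and not at 2 (2/24 = 8.3%).
- Programme target (5.2): mean SBP below 130 and mean DBP below 80.
- Reading-to-reading SD of home SBP within a person: **not in the article; assumed 6 to 12 mmHg.**
- The score is taken from one 24-reading cycle. This too is an assumption, because 6.3 names no window.

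**Step 1: an example that needs no model.** Take 3 readings of 134 and 21 of 120. The mean is (3 × 134 + 21 × 120)/24 = 2922/24 = 121.75 mmHg, which meets the systolic target. The share at or above 130 is 12.5%, so the score is 1.

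**Step 2: the mean at which 10% of readings are high.** With normally distributed readings, this mean is 130 − 1.2816 × SD. It does not depend on the number of readings or on their independence.

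**Step 3: the chance of scoring 1 in one cycle.** Let p = 1 − Φ((130 − mean)/SD). The chance is P(X ≥ 3) with X ~ Binomial(24, p), which takes readings as independent.

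| SD (mmHg) | Mean SBP for 10% high readings | p at mean 125 | P(score 1) at mean 125 | P(score 1) at mean 120 |
|---|---|---|---|---|
| 6 | 122.3 | 0.202 | 0.891 | 0.105 |
| 8 | 119.7 | 0.266 | 0.973 | 0.473 |
| 10 | 117.2 | 0.309 | 0.990 | 0.757 |
| 12 | 114.6 | 0.338 | 0.996 | 0.891 |

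On these assumptions the BP item asks for a mean SBP about 8 to 15 mmHg below the 130 mmHg limit of the programme target (130 − 122.3 = 7.7; 130 − 114.6 = 15.4). The independence assumption matters little: a correlation of 0.3 to 0.6 within each pair of readings lowers the 0.973 at SD 8 to about 0.95 to 0.96.

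**Step 4: the other direction.** A participant with mean DBP of 80 or more and at most 2 high systolic readings has not met the programme target, yet scores 0.

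**Step 5: LDL-C.** Sections 3.1.1 and 5.4 give 50, 70 and 100 mg/dL by risk under a 2025 guideline. Section 6.3 names a 2013 guideline and gives no values. The standards differ, but no misclassification rate can be calculated from the article.

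**The case against.** The strongest reply is that a burden-type BP outcome, stricter than the treatment target, can be a legitimate choice. A fixed cut-off also has a merit: section 5.2 lets targets be individualised, and controls have no programme target, so scoring against individual targets could give the arms different thresholds. BP, HbA1c and LDL-C are also analysed separately by ANCOVA (9.4), so the effect on each risk factor is not lost. All of this stands. It limits the weight of the point and shapes the remedy, but it does not explain why a score of parameters above target departs from the stated targets without a reason.

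A reader might also infer more than the article supports:

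- **That most participants who reach the BP goal would be scored as failures.** This needs the distribution of achieved SBP, which is not given. At mean 120 and SD 6 the probability is only 0.105.
- **That the treatment effect is diluted.** A stricter cut-off applied to both arms can shrink or enlarge a difference, depending on that same unknown distribution.
- **That LDL-C control is under-recorded.** Without the 2013 values in the article, the error could run either way.
- **That the systolic item also contradicts the enrolment rule.** Section 3.1.1 itself accepts two or more single office or home readings at or above 130. The systolic conflict is with the treatment target in 5.2.
- **That controls have no home readings.** Section 5 says of the control arm that "there are no scheduled tele‐touchpoints beyond those required for data collection", which leaves room for protocol-required collection. The Schedule of Activities is in supporting material that is not shown.

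**Conclusion.** The point holds as a conflict between definitions. For systolic pressure, the consequence is shown by arithmetic without any assumption: a 24-reading cycle with mean 121.75 mmHg meets the programme's systolic target and scores 1. How often this happens at a given mean rests on an assumed SD of 6 to 12 mmHg, normal readings and a single cycle. At a true mean of 125 the probability is about 0.89 to 0.996, and expecting 10% or fewer high readings needs a mean of about 115 to 122. The missing diastolic term produces errors in the opposite direction. For LDL-C, only the mismatch of standards is established.

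The weight is moderate. A formally tested endpoint cannot be interpreted as its description promises, but it is the tertiary endpoint. The primary win-ratio analysis and the sample size of 838 are untouched.

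**What to change.** Reconcile section 6.3 with sections 3.1.1, 5.2 and 5.4, or state why the scoring thresholds differ. The direct way is to reword the three items:

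- **BP:** 1 point if the mean of a home-BP cycle is SBP at or above 130 or DBP at or above 80 mmHg. Use the same fixed cut-off for every participant, regardless of individualised targets, and collect BP in the same way at baseline and week 84 in both arms.
- **LDL-C:** 1 point if at or above the risk-specific threshold in 3.1.1 (i) to (iii). Exclude item (iv) explicitly; a history of at least 190 mg/dL at any time would otherwise score 1 permanently.
- **HbA1c:** as stated.

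This changes only how the endpoint is scored. It alters no treatment target and implies no view on which target is clinically right. The cost is a change of wording. If the Schedule of Activities does not already provide a home cycle for controls, it adds at most two six-day cycles per control participant.

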### Safety Assessments

6.4

Safety assessments will include adverse events, clinical laboratory measurements (chemistry, hematology), and vital signs (systolic and diastolic blood pressure). A complete medical, surgical, and family history will be completed at the randomization visit. All laboratory test results must be evaluated by the investigator as to their clinical significance. Any observations at physical examinations or laboratory values considered by the investigator to be clinically significant should be considered an adverse event.

## Sample Size Calculation

7

Given that a comprehensive multifactorial intervention targeting intensive cardiovascular risk factor control has been associated with significant reductions in cardiovascular mortality (−57%), cardiovascular events (−59%), and hospitalizations due to heart failure (HF) in patients with diabetes [1], this study was designed using a standard win ratio test. The win ratio test incorporates both all‐cause mortality and all‐cause hospitalizations, using component‐wise hazard ratios (HRs) as effect size estimators.

For the sample size estimation, predefined hazard ratios (HR 0.90 for all‐cause death and HR 0.70 for all‐cause hospitalization) were used, targeting 90% statistical power with a two‐sided *α* = 0.05% and 5% expected attrition. Sensitivity analyses explored plausible variations in baseline event rates and component HRs to confirm robustness of the win‐ratio and power assumptions. A total of 838 participants (419 per treatment arm) will provide adequate power under these scenarios. Sample size calculations were performed in R (v1.2) using the WR package, as described by Mao et al. and Yu et al. [14, 15]. Supporting Information Material 4 summarizes the simulation scenarios and corresponding sample size estimates.

## Blinding

8

This study will be conducted as an open‐label trial. However, certain personnel will remain blinded to the randomization process. Specifically, the study sponsor, the independent Data Safety Monitoring Board (DSMB), study administrators, and personnel at the supporting organizations and vendors will be unaware of the allocation sequence.

All study data will be collected at participating sites and entered into the TAMIS‐IA platform, a secure, web‐based electronic data capture platform. Participants will be de‐identified using unique alphanumeric codes, and all data will be managed in compliance with the Brazilian LGPD. Data accuracy will be ensured through double‐entry verification, real‐time audit trails, and predefined data validation rules. Quality assurance activities will include biweekly remote audits, centralized query resolution, and continuous oversight by the Coordinating Center.

An independent DSMB composed of experts in cardiology, clinical trials, epidemiology, and biostatistics will oversee the study's safety and scientific integrity. The DSMB will remain blinded to treatment allocation and will conduct closed‐session interim reviews every 12 weeks, evaluating unblinded data for cumulative adverse events, recruitment metrics, and overall risk‐benefit profile. Predefined stopping criteria for harm, futility, or overwhelming efficacy will guide DSMB recommendations.

On the other hand, patients, study investigators, monitors, and clinical staff at the Health care Units will be aware of the allocation. To mitigate biases, the dataset will be de‐identified after data lock, ensuring that the study medication and treatment allocation are concealed from data analysts and statisticians.

## Randomization

9

### Randomization Sequence Generation

9.1

The randomization sequence will be generated using a computerized random number generator within RStudio, utilizing the *blockrand* package.

### Type of Randomization

9.2

A stratified randomization approach will be employed to ensure balance between the study arms. Stratification will be based on key demographic and clinical characteristics, including age (< 55 or ≥ 55 years), gender and prior cardiovascular disease. Within each stratum, randomization will follow a permuted block design with block sizes randomly varying between four and eight, ensuring equal representation of each intervention arm within each stratum.

### Implementation

9.3

Participant enrollment will be conducted by trained personnel at the primary health care units, who will follow eligibility criteria to identify and obtain consent from eligible individuals. These personnel will remain unaware of the allocation sequence, preserving the integrity of the randomization process.

After data blocking for analysis, the study intervention groups will be de‐identified, ensuring blinding for data analysts and maintaining the study's methodological rigor.

### Statistical Methods

9.4

All continuous variables will be presented as median and interquartile range (IQR), while categorical variables will be reported as absolute (n) and relative frequency (%).

Descriptive statistics (mean ± standard deviation, median and IQRs) will be generated for each treatment group to summarize demographic and baseline characteristics. Between‐groups comparisons will be conducted within the Intention‐to‐Treat (ITT) population to ensure that the randomization process successfully achieved balance between groups. Differences in baseline characteristics between treatment groups will be tested using a chi‐square test for categorical variables and a two‐tailed *t*‐test with treatment as a factor for continuous variables. These preliminary analyses will serve as an initial assessment of the adequacy of randomization.

The primary endpoint analysis will be performed using a win‐ratio test, which combines time to all‐cause death and the frequency of nonfatal hospitalizations. The win ratio test will follow the original methodology described by Pocock et al. [16]. Beyond hierarchical endpoint evaluation, this approach allows for the integration of multiple endpoint types. Treatment differences will be tested at an alpha level of 0.05, with a sequential procedure for controlling type 1 error. Additional covariate adjustments for time‐sensitive analyses will be performed using a Cox proportional hazards model, incorporating the randomization stratification factor. The HR for treatment groups will be reported along with the 95% confidence interval (CI).

The secondary endpoint analysis will be performed using Kaplan‐Meier survival curves, evaluating time‐to‐event data for each secondary efficacy endpoint. The log‐rank test used for the primary endpoint analysis will also be applied to secondary endpoints. Treatment differences will be tested at an alpha level of 0.05, employing a sequential procedure for type 1 error correction. Covariate adjustments for time‐dependent analyses will again be performed using the Cox proportional hazards model, with the HR and 95% CI reported.

For non–time‐to‐event secondary endpoints, including changes in metabolic and clinical parameters (blood pressure, HbA1c, LDL‐C) and patient‐reported outcomes, analyses will be performed using paired t‐tests and analysis of covariance (ANCOVA) models, incorporating baseline values as covariates. Treatment differences will be evaluated at a two‐sided alpha level of 0.05, applying the same hierarchical procedure used for time‐to‐event endpoints to control type I error. All analyses will follow the ITT principle, and sensitivity analyses will be conducted to assess the impact of missing data.

For the tertiary endpoint analysis, the study will evaluate changes in the MeTaRiSc from baseline to Week 84. Each participant will receive a score of 1 for each parameter above the target; the total score will then be divided by three, producing a weighted mean ranging from 0 to 1. A paired t‐test will compare the two treatment groups. Treatment differences will be tested at an alpha level of 0.025, using a sequential type 1 error correction procedure. Covariate adjustments will be made using a *t*‐test, incorporating the randomization stratification factor. The mean values for each treatment group (intervention vs. control) will be reported with the corresponding 95% CI.

All subgroup analyses will involve log‐rank tests and the hazard ratios (with 95% CIs) for primary and secondary efficacy endpoints. The predefined subgroups include sex, age (< 65 vs. ≥ 65 years), prior cardiovascular disease, presence of cardiovascular risk factors (diabetes, hypertension, chronic kidney disease), smoking history (active vs. significant past smoking), obesity/metabolic syndrome, and prior statin use.

The present study was designed in accordance with the NIH‐FDA Clinical Trial Protocol Template. A structured protocol and a Statistical Analysis Plan (SAP) were developed prior to participant enrollment, specifying the analytic approach for all predefined endpoints, including sensitivity and subgroup analyses.

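### The primary win ratio is described without the randomization strata; if it ignores them, the test stays valid but is slightly conservative and gives up some power

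*Protocol article*

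**What the plan says.** Section 9.2 (Type of Randomization) stratifies on characteristics "including age (< 55 or ≥ 55 years), gender and prior cardiovascular disease", and within each stratum "randomization will follow a permuted block design with block sizes randomly varying between four and eight". Three two-level factors give at least 2 × 2 × 2 = 8 strata.

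The primary test is described in three places, none of which mentions strata:

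- Section 6.1 (Primary Efficacy Endpoint) calls it a standard win ratio.
- Section 7 (Sample Size Calculation) says "this study was designed using a standard win ratio test".
- Section 9.4 (Statistical Methods) says "The win ratio test will follow the original methodology", with a reference to the source paper.

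In section 9.4 the strata appear in connection with the primary endpoint only for additional covariate adjustment, which "will be performed using a Cox proportional hazards model, incorporating the randomization stratification factor". The same factor is mentioned again for the tertiary score. The article also reports that a SAP was written before enrollment; it is not shown.

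**The concern.** Restricted randomization removes chance imbalance between arms on the stratification factors. An analysis that ignores those factors makes no use of that balance. Its usual variance still carries the between-stratum component, so the standard error is larger than the true sampling variability whenever the strata predict outcome. In an all-pairs win ratio, an older participant with prior cardiovascular disease is also compared with a younger one without it, and prognosis contributes to the result of that comparison.

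The article does say where stratification enters the analysis, for the Cox models and the tertiary endpoint, but not for the test that decides the trial. At stake is power that the trial could have from data it already collects. The validity of the conclusion is not at stake.

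**Working it through.** **The plan's own figure.** The 838 participants cannot be reproduced, because the article defers baseline event rates to a supplement. Only the last step can be checked: 796/0.95 = 837.9 and 798 × 1.05 = 837.9, so 838 fits 5% attrition under either convention. The question of strata therefore has to be answered by simulation.

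**Inputs from the article.** 419 per arm, 84 weeks, 5% attrition, HR 0.90 for death and 0.70 for hospitalization, two-sided alpha 0.05, blocks of 4 to 8 within 8 strata.

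**Assumed inputs.** Deaths 0.02–0.03 per year; hospitalizations 0.15–0.50 per year; gamma frailty with variance 0.5; prevalences 0.65 (age ≥ 55), 0.42 (one gender) and 0.20 (prior cardiovascular disease). Log rate ratios for the three factors are 0.4/0.2/0.6 (moderate; rate ratios 1.49, 1.22, 1.82) or 0.8/0.4/1.1 (strong; 2.23, 1.49, 3.00). Dropouts with no recorded death count as survivors, in both tests alike.

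**Statistics compared.** With W_k wins, L_k losses and N_k participants in stratum k:

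- Unstratified: log(W/L) over all pairs, divided by its standard error.
- Stratified: log[Σ(W_k/N_k) / Σ(L_k/N_k)] over within-stratum pairs only, divided by a standard error whose variance is summed over strata.

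**Results** (2,500 trials per row; %, unstratified / stratified):

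| Deaths, hospitalizations per year | Strata | Type I error | Power | Gain (points) |
|---|---|---|---|---|
| 0.02, 0.15 | moderate | 4.7 / 4.9 | 48.9 / 49.3 | 0.4 |
| 0.02, 0.30 | moderate | 4.1 / 4.8 | 70.8 / 71.7 | 0.9 |
| 0.03, 0.50 | moderate | 4.2 / 4.5 | 84.6 / 85.5 | 0.9 |
| 0.02, 0.15 | strong | 5.0 / 6.0 | 42.3 / 45.0 | 2.7 |
| 0.02, 0.30 | strong | 3.8 / 5.2 | 64.8 / 68.8 | 4.0 |
| 0.03, 0.50 | strong | 2.7 / 3.8 | 77.7 / 82.2 | 4.5 |

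Monte Carlo standard errors: √(0.05 × 0.95/2500) = 0.4 points for type I error, and at most √(0.25/2500) = 1 point for each power.

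**Mechanism.** Under the null, the standard deviation of the unstratified z was 0.90 to 0.98 instead of 1; for the stratified z it was 0.97 to 1.01. A standard deviation of 0.901 implies a rejection rate of 2 × [1 − Φ(1.96/0.901)] = 3.0%, and 0.981 implies 4.6%. These agree with the simulated rates within noise.

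**Second simulation, different assumptions.** 4,000 trials per scenario, 398 evaluable per arm, 3% control deaths, 46% of controls hospitalized, prevalences 0.65, 0.55 and 0.25. With rate ratios 1.5, 1.2 and 2.0, power is 84.0% unstratified and 85.6% stratified (gain 1.6). With 2.0, 1.3 and 3.0, it is 80.8% and 86.0% (gain 5.2). Under the null the unstratified test rejects in 3.4–5.0% of trials and the stratified in 4.7–5.3%.

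**Gain as sample size.** Under a normal approximation the ratio is [(z_new + 1.96)/(z_old + 1.96)]², with z the normal quantile of the power.

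- 80.8% to 86.0%: (3.040/2.831)² = 1.15, about 15%.
- 77.7% to 82.2%: (2.883/2.722)² = 1.12, about 12%.
- 84.6% to 85.5%: (3.018/2.979)² = 1.03, about 3%.

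On 838 participants, 12–15% is roughly 100 to 126; 3% is about 25.

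**Pairs dropped.** With the first set of prevalences, the within-stratum share of all pairs is (0.65² + 0.35²)(0.42² + 0.58²)(0.20² + 0.80²) = 0.19. About four fifths of pairs go, yet power does not fall in any row. The smallest stratum would hold 838 × 0.35 × 0.42 × 0.20 ≈ 25 participants, so a rule for sparse strata is needed.

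**The case against.** The strongest objection is that the article never says the win ratio is unstratified. It cites a source whose provisions on matching or stratifying by risk cannot be checked here, and weights and variance are ordinary SAP content. This stands in part: the absence of strata is the natural reading, not a stated choice. But the article does assign the stratification factor to other analyses, so the point concerns how it describes the primary test and not merely detail left out.

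The second objection is that an unstratified test after stratified randomization is legitimate and matches the test on which the trial was sized. This stands in full. A reader might infer that type I error is wrong or the primary conclusion unsafe; the figures show the opposite, since the test errs toward caution. Nor do simulated powers below 90% show the trial to be underpowered, because the event rates behind them are assumed.

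The third objection is that the gain is small and assumption-driven. With moderate strata it lies at or near simulation error. The strong scenarios need large differences between extreme strata: 2.0 × 1.3 × 3.0 = 7.8-fold in one simulation and exp(2.3) ≈ 10-fold in the other. Gains were smallest at the lowest hospitalization rate. This limits the size, not the direction.

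Fourth, the stratified test's type I error ranged from 3.8% to 6.0% in the first simulation. Both extremes lie more than two Monte Carlo standard errors from 5%, but the corresponding null standard deviations (0.973 and 1.014) imply about 4.4% and 5.3%, and the second simulation gave 4.7–5.3%. There is no clear miscalibration.

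The singular form in "incorporating the randomization stratification factor" is no ground for criticism; it can denote the combined stratum variable.

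**Conclusion.** The point holds as an efficiency improvement. The design stratifies, and the primary test is described without use of the strata. If it does ignore them, it stays valid, is slightly conservative, and loses about 0.4 to 2 points of power with modestly prognostic strata and about 3 to 5 points with strongly prognostic ones.

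The direction is secure: it follows from theory and appears in both simulations. The size is only moderately certain, because event rates, prevalences, stratum effects and frailty are all assumed. Where in the range the trial falls depends mainly on how strongly age and prior cardiovascular disease predict death and hospitalization in this population.

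**What to change.** State in section 9.4 and in the SAP that the primary win ratio is stratified by the randomization strata. Each intervention participant is compared only with controls in the same age × gender × prior-cardiovascular-disease stratum, strata are combined with Mantel-Haenszel-type weights, and the variance matches. Add a rule, fixed in advance, for collapsing sparse strata. Keep the unstratified win ratio as a sensitivity analysis. If the SAP already stratifies, one clause in the article settles the matter.

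The cost is a short text change and some programming, with no new data. There is one small downside: cross-stratum pairs are dropped, so the summary becomes a within-stratum effect that can differ slightly from the all-pairs win ratio. The choice should be settled before outcome data by arm are seen, since the two versions can give different results and the trial is open-label.
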